**Objective 3: Evaluation of the impact of the survey’s sampling frame.**

The five *microtrials* presented in Objectives 1 and 2 will be sent to phone numbers that were randomly generated (i.e. a random digit dial [RDD] approach). Objective 3’s *microtrial* will send IVR surveys to a list of de-identified phone numbers that were provided by a mobile network operator (MNO; i.e. a cell phone company) and/or which were collected from a previous household survey where consent was collected. We will compare the demographic representativeness, response rate, completion rate, and cost from the IVR survey sent using MNO provided phone numbers with the IVR surveys from Objectives 1 and 2 in order to assess the effect of the sampling frame on these key survey metrics.

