**V. Study Procedures**

A. Recruitment Process:

1. ***Describe how you will identify, approach, and inform potential participants about your study. Include details about who will perform these activities and what their qualifications are.***

For all objectives, there will be no face-to-face or “in-person” interactions between study team members and research participants. We will work closely with in-country collaborators to obtain necessary national approvals for the study, including for the recruitment strategies outlined below.

For objectives 1, 2, and 4 the sampling of participants will be done using RDD. RDD is a method often used to select individuals to participate in a telephone survey through computer-facilitated random generation and dialing of digits that may comprise active telephone numbers. For objective 3, IVR surveys will be sent to a random sample of de-identified mobile phone numbers that were provided by a mobile network operator (MNO; i.e. a cell phone company or numbers list vendor) and/or which were collected from a previous household survey, where permission for re-contact was provided.

For all objectives, potential respondents will first receive a single SMS notification indicating that they will be sent a mobile phone survey shortly. The SMS will contain brief information on the survey’s purpose, the expected time commitment, and the survey’s sponsoring agency. An IVR survey will then be sent once to the same randomly generated mobile phone number where participants will be able to consent to the survey or refuse their participation (or CATI for microtrial #7). SMS notifications and IVR surveys will be sent by a mobile phone survey provider (e.g., VOTOmobile, a company that specializes in delivering IVR surveys and deploying RDD approaches globally) and who will be sub-contracted by investigators from JHU. For microtrials that contain a call center (*microtrials #5 and 7),* operators will be trained in human subjects research by the in-country partner. Training will include procedures on recruitment, consent, and interviewing techniques.

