This microtrial seeks to examine whether the timing of incentive delivery (either given before the survey or afterwards) has an effect on contact, response, and/or completion rates. Participants will be randomized to one of three study arms: 1) no incentive, 2) a pre-paid airtime incentive; where 20-40%% of the total incentive (X) is sent to the respondent’s mobile phone after the sensitizing SMS and prior to initiation of the survey, and with the remaining 60-80% being sent after the survey’s completion (i.e. all questions answered), or 3) a promised incentive where 100% of the incentive amount is sent to the respondent’s mobile phone after the IVR survey is completed. With existing technology, the minimal amount of airtime that can be transferred is 1 USDThe total incentive amount (X) in this microtrial will be the incentive amount from *microtrial* #1 that produced the highest response and completion rates.

*Microtrial #3*- Evaluation of incentive structure

This microtrial seeks to examine whether the incentive structure (a fixed incentive amount or a lottery-based incentive) has an effect on response and completion rates. Respondents will be randomized to one of three study arms: 1) no incentive, 2) a fixed airtime incentive delivered after survey completion where the amount of the incentive is determined by *microtrial* 1, and 3) a lottery airtime incentive of an amount five times greater than the amount in the second study arm; where the odds of winning the lottery are 1:20.

Objective 2: Evaluation of the Surveys Introduction

*Microtrial #4*- Evaluation of content and voice of IVR survey’s introduction

This microtrial seeks to examine whether the content of the IVR survey’s introduction (motivational vs informational) and the survey’s narrative voice (male vs female) has an effect on contact, response, and/or completion rates. Participants will be randomized to one of four study arms with varying survey introduction content and voices: 1) male voice, informational content, 2) male voice, motivational content, 3) female voice, informational content, and 4) female voice, motivational content. Participants in each study arm will receive the same incentive.

*Microtrial #5*- Evaluation of a human operator IVR survey introduction

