This microtrial seeks to examine whether the survey introduction’s modality (human operator versus those who receive an IVR survey introduction) has an effect on survey response and completion rates. Participants will be randomized to one of two arms: 1) a human will call the RDD-generated mobile phone number and read the survey’s introduction. The operator will answer any questions the participant may have, consent the participant and then patch the participant into the IVR survey, and 2) the participant will receive a IVR survey with a survey introduction in IVR format and similar to the previous *microtrials*.

Objective 3: Evaluation of the Sampling Frame

*Microtrial #6*- Evaluation of the sampling frame of mobile phone numbers

This microtrial seeks to examine whether the source of the mobile phone numbers has a differential effect on the IVR survey’s response and completion rates. The previous five *microtrials* relied on a RDD sampling frame. In this microtrial, we will obtain a de-identified list of mobile phone numbers from either a mobile network operator or from a previously conducted household survey where participants had consented to be contacted for additional studies. Participants will be sent an IVR survey with the top performing survey introduction (results from microtrials 4 and 5) and the top performing incentive (microtrials 1-3).

Objective 4: Evaluation of Survey Modality

*Microtrial #7*- Evaluation of CATI and IVR survey metrics

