| **Notes** | -First microtrial to be conducted  -Incentive given after completion of IVR survey (Post-IVR) | -Incentive amount will range from X to 2X | -1:20 odds of winning lottery; incentive is 5 times amount in fixed incentive arm | -Provide same incentive in each arm  -The only difference in the questionnaire is the survey’s introduction. | -Human intro is a call center that asks participants if they wants to participate and if so, patches them into an IVR  -Provide same incentive in each arm | -Incentive and survey introduction used are top performers from microtrials #1-4 | - IVR arm will receive IVR survey first, followed by CATI survey 7 days later  -- CATI arm will receive a CATI first followed by an IVR survey 7 days later. |

Abbreviations: CON, contact rate; MNO, mobile network operator; RR, response rate, COMP, completion rate; R, refusal rate

***2. Describe the number and type of study visits and/or contacts between the study team and the participant, how long they will last, and where/how they will take place.***

There will be no face-to-face (i.e. in-person) contact between participants and the study staff. All interactions with research participants will be through the participant’s personal mobile phone. Participants will be randomly selected from a list of randomly generated mobile phone numbers (microtrials 1-5) or from a pre-defined and de-identified list of mobile numbers provided by a MNO or household survey. The selected mobile phone number will be sent one text message that alerts the potential participant about the upcoming survey. For all *microtrials* except for *microtrial #7,* participants will be sent one MPS. If a participant decides to answer the MPS, the time to complete the survey should be no more than 30 minutes. For *microtrial #7*, participants will be sent a CATI and IVR survey separated by seven days. In a sub-sample of participants who either refused to participate in the IVR survey, did not initiate the survey, or who did not complete the survey, participants will be called back by a human operator to understand reasons for their not fully participating in the survey. This interview is expected to take no more than 30 minutes. Therefore, participants may have up to three contacts with the mobile phone survey. For each contact, a verbal consent will be taken.

***3. Describe the expected duration of the study from the perspective of the individual participant and duration overall.***

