To minimize risks associated with answering questionnaires, participants will be informed that they do not need to answer any question that they feel uncomfortable with and that their participation in the IVR survey is voluntary. Participants will be informed and allowed to end their participation at any time. To minimize risk of confidentiality breach, we have employed several safeguards. First, the IVR survey does not collect any personal identifying information aside from the mobile phone number (date of birth and name are not collected). Following completion of the IVR surveys, the PI will download data from the VOTOmobile platform and permanently delete the column containing mobile phone numbers. After this step, there will be no record of mobile phone numbers associated with the IVR survey.

No names will be used in any reports or documents stemming from this research protocol. Study staff who are involved with microtrial 5 and microtrial 7 (human operators) and who call back participants to understand reasons for their non-participation will be trained in human research ethics.

*D.* ***Describe the research burden for participants, including time, inconvenience, out-of pocket costs, etc.***

Overall, participants will spend up to 30 minutes for each mobile phone survey in the seven microtrials. For microtrial seven, participants receive two mobile phone surveys. This amount of time may be inconvenient for participants. In a sub sample of microtrial participants, we will call individuals to understand reasons for their non-participation; at most, this would be 30 minutes. The costs of airtime associated with answering the MPS will be borne by the study team and transferred directly to respondents within 24 hours of their completing a survey. VOTOmobile has experience with issuing airtime credit transfers across multiple mobile network providers. Therefore, participants will not incur any out-of-pocket expenses as part of their participation in the study.

*E.* ***Describe how participant privacy will be protected during data collection if sensitive questions are included in interviews.***

The survey questions are administered over a telephone call. Therefore, it will be difficult for people not associated with the study to hear and understand the survey questions and participant’s responses.

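### The text and Table 2 disagree on whether microtrial 6 can use the human-operator introduction; if the text governs and the operator is chosen, Objective 3 confounds sampling frame with introduction mode

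*Protocol*

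**What the plan says.** In the protocol's Microtrial Designs section (V.C), the description of microtrial 6 fixes its introduction by a rule: "Participants will be sent an IVR survey with the top performing survey introduction (results from microtrials 4 and 5"). The Notes row of Table 2, in the microtrial 6 column, gives a different source: "Incentive and survey introduction used are top performers from microtrials #1-4".

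The two introduction trials differ in kind. For microtrial 4, "Participants will be randomized to one of four study arms with varying survey introduction content and voices"; all four are recorded. For microtrial 5, "Participants will be randomized to one of two arms: 1) a human will call the RDD-generated mobile phone number and read the survey’s introduction". In that arm the operator also takes consent and then transfers the person into the automated survey. The other arm gets an automated introduction.

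Four other places bear on this:
- Recruitment (V.A) begins an operator-training sentence "For microtrials that contain a call center" and names microtrials 5 and 7.
- Consent (V.B) describes consent taken verbally by an operator for microtrials 5 and 7; otherwise consent is a key press.
- Survey Delivery (V.C) excepts only microtrial 5 from the pre-recorded introduction.
- Risks (VII.C) provides ethics training for "Study staff who are involved with microtrial 5 and microtrial 7 (human operators"), besides the staff who make follow-up calls.

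Objective 3 (III.A) states what microtrial 6 is for: "We will compare the demographic representativeness, response rate, completion rate, and cost from the IVR survey sent using MNO provided phone numbers". The comparator is the set of IVR surveys in Objectives 1 and 2.

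**The concern.** Whether microtrial 5 counts decides whether a call centre can appear in microtrial 6. That affects how the survey is delivered and how consent is taken, so a later analysis plan cannot settle it.

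It also affects what Objective 3 estimates. The protocol's completion rate has refusals in its denominator, and its response rate has refusals and people who answered but did not engage. Introduction and consent mode act at exactly these steps. If microtrial 6 uses an operator and most of its comparators do not, a difference between list-based and random-digit numbers cannot be separated from a difference between operator and recording. Cost is a named outcome and would include operator labour that the other arms did not incur.

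**Working it through.** **1. The two rules side by side.**

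| Source | Introductions eligible for microtrial 6 | Operator eligible? |
|---|---|---|
| Text, microtrial 6 | microtrials 4 and 5 (4 + 2 = 6 arms, one with an operator) | yes |
| Table 2 note | microtrials 1 to 4 (recorded only) | no |

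Table 2's own column headings put the human introduction in microtrial 5, so its note excludes the operator by its wording.

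**2. How much of the comparator would match.** Randomised RDD arms in Objectives 1 and 2, leaving out the baseline survey: 3 + 3 + 3 + 4 + 2 = 15. One of them (microtrial 5, human arm) has an operator; 15 − 1 = 14 do not.

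**3. The plan's sample size, to fix the denominator.** Inputs from section III.B: 30% v 40% completion, alpha 0.05 (two-sided assumed, since sidedness is not stated), power 80%.
- Without continuity correction: n = [1.960·√(2·0.35·0.65) + 0.842·√(0.30·0.70 + 0.40·0.60)]² / 0.10² = 356.
- With continuity correction: 376, the protocol's figure.
- 376 / 0.30, rounded up, is 1254 consented per arm.

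The protocol uses 376 as a number of completers, so about 1254 is the number at risk of completing. I use 1254 below.

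**4. Chance that the operator is selected when introduction mode has no effect.** The text gives no deciding metric, margin or default, so the result depends on the reading.
- *Nominal lead in microtrial 5 alone, one metric.* X and Y both Binomial(1254, 0.30): P(X > Y) = 0.491, P(X = Y) = 0.017. With ties split, 0.491 + 0.017/2 = 0.50. By symmetry this does not depend on n.
- *Lead on both response and completion in microtrial 5.* 1/4 + arcsin(ρ)/(2π), with ρ the correlation between the two differences: 0.25 at ρ = 0, 0.33 at ρ = 0.5, 0.50 at ρ = 1.
- *Single best of all six arms on one metric.* 1/6 = 0.17 (simulation: 0.167). This assumes equal rates across two trials not randomised against each other.
- *Table 2 rule.* 0.

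**5. What a mismatch could do.** Illustration only: suppose the frame has no effect, the operator raises completion from 30% to 40% (the protocol's own design difference), the arms are of equal size and all 15 are pooled. The RDD rate is (14 × 0.30 + 1 × 0.40)/15 = 0.307. Microtrial 6 shows 0.40. The apparent frame effect is 0.40 − 0.307 = 0.093, about 9 points, all of it due to the operator. Against microtrial 5's human arm alone it is 0.40 − 0.40 = 0.

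**6. Would a significance threshold prevent this?** If the operator were adopted only after a two-sided 0.05 test in its favour, adoption would be about 2.5% under no effect but over 99.9% at a true 10-point advantage with 1254 per arm. The threshold limits chance adoption. It does not remove confounding when the operator effect is real.

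**The case against.** A reader might infer that the call-centre introduction will be adopted half the time by chance. The document does not support that as a general statement. The 0.50 needs the text to override Table 2, microtrial 5 to decide alone, a single metric to decide, and a bare nominal lead to suffice. It is the top of the range. Moreover, under no effect the operator would not distort response or completion; only cost would clearly change.

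A reader might also infer that the missing threshold is the main fault. The protocol says arms will be compared at alpha 0.05, and how a winner is declared may be left to an analysis plan that is not shown. The rule after microtrial 1 does have a fallback to the lower incentive, but its trigger, an appreciable difference, is not quantified either. The threshold is secondary.

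Nor do the call-centre sections prohibit an operator in microtrial 6. They leave it out, and these lists are not strictly complete: Survey Delivery does not except microtrial 7 from the recorded introduction, although that trial includes operator interviews.

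Table 2 could itself be the slip. The Objective 2 overview in III.A numbers the human-operator trial as 4, and on that numbering a range of 1 to 4 would include it. The document does not settle which rule was intended.

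Finally, a mismatch of introduction is not peculiar to the operator. Microtrial 4 has four different recordings, the introduction used in microtrials 1 to 3 is not stated, and Objective 3 does not commit to pooling all 15 arms.

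All of this stands. It narrows the point to the contradiction and its consequence for the comparator, and it is why a matched comparator is needed under either rule.

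**Conclusion.** The point holds as a contradiction between two current statements of microtrial 6's introduction, one admitting a human operator and one not. The sections on operators, consent and delivery provide for the second but do not forbid the first.

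The consequence is conditional. If the text governs and the operator is selected, frame is confounded with introduction and consent mode in 14 of 15 randomised RDD arms, and operator cost is added. Under no effect of introduction mode, selection has probability about 0.17 to at most 0.50 over the readings examined, and 0 under Table 2. The 9-point distortion above is an illustration that rests on pooling and on a true 10-point operator effect; it is not a forecast.

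The protocol is wrong as written and should be corrected, because Objective 3's comparison on response, completion and cost depends on it.

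**What to change.** Reconcile the microtrial 6 description with the Table 2 note.
- *Simplest version:* remove microtrial 5 from the text rule, so that the introduction comes from the recorded ones in microtrial 4. This agrees with Table 2 and with the recruitment, consent, delivery and risk sections. It costs one sentence and no participants. The small downside is that the list frame is not tested with an operator introduction, even if that proves better.
- *If the sponsor wants microtrial 5 to count:* correct Table 2, extend the call-centre and operator-consent provisions to microtrial 6, and state how the winner is declared (metric or metrics, criterion, and what applies when there is no clear difference).

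In either case, state that the primary Objective 3 frame comparison is against the RDD arm or arms that used the same introduction as microtrial 6, and the same incentive where such an arm exists. A comparison with all RDD arms can be kept as descriptive. The price is a smaller comparator group and so less precision than pooling would give.

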This sample size is calculated based on the kappa statistic. With assumption of kappa= 0.75, a margin of error of 0.05%, an alpha of 0.05, and the proportion of positive responses=0.3, 405 participants who have completed the survey per study arm are needed. Adjusting for a 20% loss to follow-up from the first and second mobile phone survey and a 30% baseline completion percentage, 1688 participants who consented will be enrolled per arm and per country, for a total of 3376 participants across the two arms per country. With two arms and 4 countries, a total of 13,504 participants who provide consent across the four studies are needed.

Total Sample Size

For the baseline survey and seven microtrials, in each country, a total of 23,773 individuals who have consented to an MPS survey will be needed to fulfill a sample size of 6926 individuals who completed an MPS survey per country. As this protocol is being implemented in four countries, the overall sample size is 95,092 individuals who have consented to an MPS survey and 27,704 who completed a MPS survey

**Table 1.** Number of participants who consent to and complete a mobile phone survey per country

|  | **Col. A** | **Col. B** | **Col. C^*^**  [(Col B*100)/0.30] | **Col. D**  [Col A*Col B] | **Col. E**  [Col A*Col C] |
| --- | --- | --- | --- | --- | --- |
|  | # of study arms | N participants who completed survey per study arm | N participants who consented per study arm | Total N participants who completed survey | Total N participants who consented |
| **Objective 1** |  |  |  |  |  |
| *Baseline* | 1 | 100 | 334 | 100 | 334 |
| *Microtrial #1* | 3 | 376 | 1254 | 1128 | 3762 |
| *Microtrial #2* | 3 | 376 | 1254 | 1128 | 3762 |
| *Microtrial #3*** | 3 | 376 | 1254 | 1128 | 3762 |
| **Objective 2** |  |  |  |  |  |
| *Microtrial #4* | 4 | 376 | 1254 | 1504 | 5016 |
| *Microtrial #5* | 2 | 376 | 1254 | 752 | 2508 |
| **Objective 3** |  |  |  |  |  |
| *Microtrial #6* | 1 | 376 | 1254 | 376 | 1254 |
| **Objective 4** |  |  |  |  |  |
| *Microtrial #7* | 2 | 405 | 1688 | 810 | 3376 |
| **Total** |  |  |  | 6926 | 23,773 |

* For microtrial 7, we adjust for a 20% loss to follow-up from the first and second mobile phone survey.

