This microtrial seeks to examine whether the survey’s modality (IVR versus CATI) has a differential effect on the survey’s response and completion rates and to assess the ‘inter-modal reliability’. Participants will be randomized to one of two arms: 1) IVR then CATI or 2) CATI then IVR. Participants in the first study arm will receive an IVR survey first, followed by a CATI survey 7 days later. Participants in the second study arm will receive a CATI survey first followed by an IVR survey 7 days later. At initial enrollment, participants will be clearly explained that they are being enrolled in a microtrial where they will be contacted twice. The questionnaires used in both study arms will the same. This crossover design will allow for an assessment of response consistency, adjusted for the risk of ‘priming’ after exposure to the prior modality. This is the only *microtrial* that has participants answer two NCD surveys. The amount/timing/structure of incentive will be guided by the first three *microtrials*; where the incentive that yielded the highest response and completion rates will be provided to all participants in *microtrial* #7.

Follow-up of Non-response, Refusals, and Incomplete Interviews

For participants who were selected for the seven *microtrials,* a random sub-sample of participants who did not initiate the IVR survey, refused to participate, or partially completed an IVR survey, will be called back by a human operator using the same telephone number that was associated with the IVR. The study team will attempt to reach individuals up to three times. Unreached follow-ups will be documented. If successfully reached, the team will consent and interview participants to explore reasons for participant’s non-response, refusal, or incomplete surveys using a semi-structured guide (See Appendix 2). Demographic information from non-responders, refusals, and incomplete surveys will also be collected and examined in relation to the distribution of those who fully complete the survey.

**Table 2.** Study designs for Microtrials

|  | **Microtrial#1**  **Incentive Amount** | **Microtrial#2**  **Incentive Timing** | **Microtrial#3**  **Incentive Structure** | **Microtrial#4**  **IVR Intro features** | **Microtrial#5**  **IVR vs Human Intro** | **Microtrial#6**  **Sampling frame** | **Microtrial#7**  **Survey Modality** |
| --- | --- | --- | --- | --- | --- | --- | --- |

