***4. Provide a brief data analysis* plan *and a description of variables to be derived.***

The contact rates, response rates, and completion rates will be tabulated for each of the microtrials by study arm; where contact, response, and completion rates are defined as:

The contact, response, and completion proportions^[[1]](#footnote-1)^ will be tabulated for each of the *microtrials* and by study arm where contact, response, and completion are defined as:

$$Contact Rate= \frac{CI+PI+R}{CI+PI+R+(NC+U)}$$

$$Response Rate= \frac{CI+PI}{CI+PI+R+NC}$$

$$Completion rate= \frac{\mathrm{CI}}{CI+PI+R}$$

**CI** (Complete Interview): a respondent that answered all applicable questions

**PI** (Partial interview): a respondent who consented to the survey but did not answer all questions

**R** (Refusal): a respondent who: 1) did not consent to the survey, or 2) formally withdrew during the survey

**NC** (Non-contact): a working phone number where the respondent picked up but did not engage with the survey. This is assessed by looking at the system log for time spent on the survey

**U** (Unknown): a phone number that cannot be determined whether it is a working phone number (the respondent did not pick up the phone) or not (the phone number is not eligible)

Respondents who report being less than 18 years old are considered ineligible. Ineligible respondents are excluded from the equations for contact, response, and completion rates.

Contact, response, and completion proportions will be compared by study arm for each microtrial and by incentive group. *A priori, a*n alpha of 0.05 will be used for hypothesis testing.

Partially completed surveys will be tabulated and stratified by both the question number, and the question content due to the randomization of NCD topic modules. Additionally, the average time spent answering, the number of “Don’t know” or “Refuse to answer” responses, and the number of times the question was repeated will be calculated for both the chronological question number and question content and stratified by study arm. For microtrial #7, test for agreement in survey responses between the survey modalities will be assessed using Cohen’s Kappa.

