In microtrial #7, participants will be asked to answer two surveys (IVR and call center [CATI]) composed of the same questions so that question validity can be assessed. For example, analyses will be conducted to observe whether some people may be more likely to report unhealthy habits when taking the automated IVR survey as compared to a call center because the human element is removed in an IVR survey.

Risk factor data will be collected and stored from other microtrials. This data will be compared to publically available results and national estimates to help determine if the protocol’s mobile-collected risk factor’s prevalence are similar to national estimates of household collected data. This will help answer whether the protocol’s mobile phone sample is as healthy, or unhealthy, as the traditionally administered surveys.

*5.*  ***Describe whether you are collecting or storing personal identifiers, and if yes, why you need them, and when and how you plan to dispose of them. Signatures on consent forms are considered to be identifiers.***

We will not collect personal identifiers via the consent process. Mobile phone numbers that were randomly generated are the personal identifiers. Because of the nature of the trial, the mobile phone numbers are needed to generate data. While phone numbers will initially be logged in the VOTOmobile platform alongside the data collected, immediately after each microtrial has been completed, the PI will download the database from the VOTOmobile platform and permanently delete the column containing mobile phone numbers. Phone numbers need not be retained for purposes of the study. No other potentially individually identifying data will be collected.

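### Microtrial 7 promises priming-adjusted consistency and question validity, but Cohen's kappa is neither order-adjusted nor directional, and rates by arm are not limited to the first contact

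*Protocol*

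**What the plan says.** The description of Microtrial #7 (Protocol V.C, Microtrial Designs) randomises participants to IVR followed 7 days later by CATI, or to the reverse, with the same questionnaire both times. It then says: "This crossover design will allow for an assessment of response consistency, adjusted for the risk of" priming by the earlier mode.

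The data analysis plan (V.C.4) gives two methods that apply. For rates, contact, response and completion "proportions will be compared by study arm for each microtrial". For answers, a "test for agreement in survey responses between the survey modalities will be assessed using Cohen"'s kappa. No order or period term, order-specific kappa or restriction to the first contact is mentioned.

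The same section says the questions are asked twice "so that question validity can be assessed". As its example it promises analyses of whether people report more unhealthy habits to the automated survey than to an interviewer. It names no method for these.

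The sample size (III.B, Microtrial 7) rests on kappa alone: "With assumption of kappa= 0.75, a margin of error of 0.05%, an alpha of 0.05, and the proportion of positive responses=0.3", from which "405 participants who have completed the survey per study arm are needed".

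Table 2 labels the two arms CATI and IVR. Its notes row gives both modes to each arm and names each arm by the mode received first.

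**The concern.** Objective 4 is the IVR versus CATI comparison. Kappa on paired answers measures how often they match beyond chance. It is unchanged if the two modes are swapped, so it cannot show which mode draws more reports of unhealthy habits, and it does not separate an effect of mode from an effect of having been asked a week earlier. Randomising the order makes that separation possible, but the named statistic does not carry it out.

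Agreement between two self-reports is also not validity. Microtrial 7 has no reference standard, and disagreement includes real change over 7 days.

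For rates, the arms are sequences. Comparing them contrasts the modes cleanly only at the first contact. Later contacts are selected: the sample size allows for loss between the two surveys, and the Survey Delivery section sends no further survey to people who refused or opted out. At stake is whether the trial's headline agreement and rate figures answer the mode question at all.

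**Working it through.** **1. The stated sample size.** Inputs from III.B: kappa k = 0.75, proportion positive p = 0.30, two-sided alpha 0.05. The margin is printed as 0.05%; only m = 0.05 on the kappa scale reproduces the figure (0.05% taken literally needs about 8.09 million).

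Large-sample variance of kappa with equal margins, times n:

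v = (1−k)[(1−k)(1−2k) + k(2−k)/(2p(1−p))] = 0.25 × [0.25 × (−0.5) + 0.9375/0.42] = 0.5268

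n = 1.96² × 0.5268/0.05² = 809.45, so 810 in total and 405 per arm. Inflation: 405/0.80/0.30 = 1687.5, so 1688. Both stated figures reproduce, and 405 per arm does so only if both orders are pooled.

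**2. Precision by order.**
- Pooled, n = 810: 1.96 × √(0.5268/810) = 0.050.
- One order, n = 405: 1.96 × √(0.5268/405) = 0.071.
- Difference between the two order-specific kappas: 1.96 × √(2 × 0.5268/405) = 0.100. There is 80% power only for a true difference of about 0.143.

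**3. Kappa and direction.** Cells are in the order both yes / IVR only / CATI only / both no, with mean prevalence 0.30 and 10.5% discordant.
- 0.2475/0.0525/0.0525/0.6475: observed agreement 0.895, chance agreement 0.58, kappa = 0.315/0.42 = 0.75. The mode difference is zero.
- 0.2475/0.105/0/0.6475: margins 35.25% and 24.75%, chance agreement 0.5745, kappa = 0.3205/0.4255 = 0.753. The mode difference is 10.5 points. This is the extreme case, with all discordance one way.

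**4. Kappa and priming.** An 8-point shift is assumed, with 10.5% discordance.

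| Truth | Kappa, each order | Pooled kappa | Order-adjusted IVR−CATI | Second minus first |
|---|---|---|---|---|
| Mode effect only | 0.752 | 0.752 | 8 points | 0 |
| Priming only | 0.752 | 0.750 | 0 | −8 points |
| Neither | 0.750 | 0.750 | 0 | 0 |

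The order-adjusted difference is the mean of the two within-arm IVR−CATI differences. It tells the three cases apart; kappa, whether pooled or by order, does not.

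**5. What the planned sample supports.** With 810 pairs and 10.5% discordance, the order-adjusted paired difference has half-width 1.96 × √(0.105/810) = 2.2 points and is detectable at 80% power from about 3.2 points.

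**6. Rates by arm.** All response rates here are assumptions: 10,000 numbers per arm, first-contact response 10% for IVR and 30% for CATI, and 80% at second contact among first-contact responders.
- First contact only: a 20-point difference.
- Both contacts, by arm: (1000+800)/11000 = 16.4% against (3000+2400)/13000 = 41.5%, about 25 points.
- Both contacts, by mode (which the protocol does not propose): IVR (1000+2400)/13000 = 26.2% against CATI (3000+800)/11000 = 34.5%, about 8 points.

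If instead each mode kept the same completion rate at both contacts, with IVR at 30% and CATI assumed at 40%, 50% or 60%, both arms would average 35%, 40% or 45% and the difference would be zero. Including second contacts can therefore inflate, shrink or cancel the mode effect.

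**The case against.** A reader might infer that the protocol has no directional analysis and would miss a large mode effect. The text does not support that: V.C.4 promises analyses of whether people report more unhealthy habits on IVR. What is open there is the method and the handling of order, and model detail may sit in an SAP that is not shown.

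A reader might also infer that the protocol pools both contacts and so dilutes the mode effect on response. It never says so. Table 2 names the arms by the first mode, and read that way the comparison by arm is a valid, randomised, unprimed contrast. Step 6 shows that the direction of any bias depends on assumed rates.

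Two further points are fair. The priming sentence speaks of what the design allows, which is true of a randomised order, and it concerns response consistency rather than rates. Elsewhere the protocol already calls the aim inter-modal reliability.

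What stands does not depend on missing SAP detail. The protocol itself names a statistic that does not make the adjustment it advertises, sizes the microtrial for that statistic pooled over order, uses the word validity where none can be shown, and applies a by-arm rule to arms that each receive both modes.

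**Conclusion.** The point holds in this limited form. As stated, Cohen's kappa gives neither priming-adjusted consistency nor the direction of a mode effect. A kappa of about 0.75 at 30% prevalence is compatible with a mode difference anywhere from zero to 10.5 points; the upper end is an extreme case that needs no discordance at all in one direction. The planned ±0.05 belongs to a kappa pooled over order, against about ±0.071 within an order. These figures rest on the protocol's own kappa and prevalence, on reading the margin as 0.05, and on 405 participants per arm completing both surveys.

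For rates, the defect is an unstated restriction to the first contact, not a demonstrated bias. The word validity is unsupported on the page. The design is sound and the planned sample is adequate for the paired analysis, so the plan should be amended, but nothing in the conduct of the microtrial has to change.

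**What to change.** 1. State that IVR versus CATI contrasts in contact, response, completion and refusal use the first contact only.
2. Keep the pooled kappa as the estimate the microtrial was sized for. Also report kappa by order, with its expected half-width of about 0.071. This shows whether agreement depends on order; it does not give direction.
3. For the differential-reporting question, estimate the paired IVR−CATI difference with mode and period terms, for example as the mean of the two within-arm differences, or by GEE or conditional logistic regression. Report the first-contact randomised prevalence contrast beside it, since that contrast cannot be affected by priming from an earlier survey.
4. Replace question validity with inter-modal reliability and differential reporting.

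The cost is analysis wording, with no extra participants or calls. The price is precision. Order-specific kappas are wider than the pooled one. The first-contact prevalence contrast is wider than the paired difference: with 1688 × 0.30 ≈ 506 completers per arm (assuming 30% completion in both modes) and prevalence 0.30, its half-width is 1.96 × √(2 × 0.21/506) = 5.6 points, against 2.2 for the paired estimate. It also reflects any difference in who answers each mode, so it supports the paired estimate and does not replace it.
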